Appendix 6 - EORTC QLQ – GI.NET21…………………………………………………………..20

# STUDY SUMMARY

| **Chief Investigator** | **[name]**  Head of Pancreatic Surgery  IRCCS Ospedale San Raffaele  [name]  [contact]  Email: [[contact]](mailto:[contact]) |
| --- | --- |
| **Study Coordinator** | **[name]**  Pancreatic Surgery Division  IRCCS Ospedale San Raffaele  [name]  [contact]  Email: [[contact]](mailto:[contact])  **[name]**  Pancreatic Surgery division  IRCCS Ospdele San Raffaele  [name]  [contact]  Email: [[contact]](mailto:[contact]) |
| **Study Title** | **A Prospective Evaluation of the Management of Sporadic Asymptomatic Nonfunctioning Pancreatic Neuroendocrine Neoplasms ≤ 2 cm** |
| **Short title** | **Asymptomatic Small Pancreatic Endocrine Neoplasms (ASPEN study)** |
| **Study Design** | Prospective international multicentre cohort study |
| **Study Patients** | **Inclusion criteria**  • Age > 18 years  • Individuals with asymptomatic sporadic NF-PNEN ≤ 2 cm  • Diagnosis has to be proven by a positive fine-needle aspiration (FNA) or by the presence of a measurable nodule on high-quality imaging techniques that is positive at 68Gallium DOTATOC-PET scan or Octreoscan.  • Patients who undergo surgery for NF-PNEN<2cm within 12 months. In these cases, diagnosis has to be proven by histological confirmation of NF-PNEN  • Informed consent  **Exclusion criteria**  **•** NF-PNEN > 2 cm of maximum diameter  • Presence of genetic syndrome (MEN1, VHL, NF)  • Presence of symptoms (specific symptoms suspicious of a clinical syndrome related to hypersecretion of bioactive compounds or unspecific symptoms) |
| **Research Aim** | To evaluate the most appropriate management of sporadic asymptomatic non-functioning pancreatic neuroendocrine neoplasms (NF-PNEN) ≤ 2 cm |

# BACKGROUND

Nonfunctioning pancreatic neuroendocrine neoplasms (NF-PNEN) are rare tumors that exhibit a wide heterogeneity of aggressiveness. The current World Health Organization (WHO) classification identified three categories of NF-PNEN (NF-PNEN-G1, NF-PNEN-G2, and NF-PNEC-G3) based on Ki-67 value [^1^](#_ENREF_1). Indications for surgery include the presence of a localized NF-PNEN in the absence of distant metastases as curative resection of these tumors is associated with favourable prognosis especially for low grade [^2-4^](#_ENREF_2).

In the last decade a dramatic increase in diagnosis of small, incidentally discovered, NF-PNEN was observed[^5^](#_ENREF_5) [^6^](#_ENREF_6). Several studies highlighted the role of incidental diagnosis as a powerful prognostic factor for NF-PNEN[^7^](#_ENREF_7) [^8^](#_ENREF_8). Moreover, other investigators observed a clear relationship between the tumor diameter and low risk of malignancy and systemic progression.[^9-11^](#_ENREF_9).

In particular, a tumor size ≤ 2 cm seems to be associated with a negligible risk of disease recurrence and with a very low incidence of aggressive features such as lymph node involvement[^4^](#_ENREF_4) [^12^](#_ENREF_12).

On this basis, the European Neuroendocrine Tumor Society (ENETS) proposed a “wait and see” approach for small NF-PNEN when incidentally discovered[^13^](#_ENREF_13). Since then, various series evaluated the safety of a conservative management for small, sporadic, incidentally diagnosed, NF-PNEN[^14-19^](#_ENREF_14).

After a median follow-up of 28-45 months, all the studies confirmed that an intensive surveillance for incidental and small NF-PNEN is safe in selected cases. None of the patients in the observational group deceased for disease or had disease progression when lesions were less than 2 cm. Nevertheless, available data are based only on retrospective series with a significant heterogeneity of inclusion criteria and different tumor diameter cut-off^14-18^ and the appropriate management of this entities (surveillance versus surgery) is still a matter of debate.

# AIM

To evaluate the most appropriate management of sporadic asymptomatic NF-PNEN ≤ 2 cm

# STUDY DESIGN

The study is designed as a prospective international (including also non-European institutions) multicentre cohort study, which will be coordinated by the Pancreatic Surgery Unit of San Raffaele Scientific Institute (Lead Study Centre) under the auspices of the European Neuroendocrine Tumor Society (ENETS).

The study duration is 6 years, patients will be recruited for 5 years from December 2016 to December 2021, with a follow up of 1 year at least (end of the study: December 2022). After 2 years of recruitment an interim analysis will be performed in December 2018. San Raffaele Scientific Institute will be the lead centre from where the international study will be managed and coordinated. Participating study centre will identify, recruit patients and will send pseudoanonimised data of patients to the lead centre, which is responsible for statistical analysis, storing and controlling data. The research database will be managed and analysed by the Lead Study centre research team. Study participation is voluntary, there will be no reimbursement for patients.

# STUDY POPULATION

## 5.1 Population

This study enrols individuals with sporadic incidentally discovered NF-PNEN ≤ 2 cm.

## 5.2 Inclusion Criteria

- Age > 18 years
- Individuals with asymptomatic sporadic NF-PNEN ≤ 2 cm
- Diagnosis has to be proven by a positive fine-needle aspiration (FNA) or by the presence of a measurable nodule on high-quality imaging technique (CT or MR) that is positive at ^68^Gallium DOTATOC-PET scan or Octreoscan.
- Patients who undergo surgery for NF-PNEN<2cm within 12 months. In these cases, diagnosis has to be proven by histological confirmation of NF-PNEN
- Informed consent

**5.3 Exclusion Criteria**

- NF-PNEN > 2 cm of maximum diameter
- Presence of genetic syndrome (MEN1, VHL, NF)
- Presence of symptoms (specific symptoms suspicious of a clinical syndrome related to hypersecretion of bioactive compounds) or unspecific symptoms

**5.4 Sample Size Calculation**

Based on a reported incidence rate of PNEN of 0.4/100.000 inhabitants[^5^](#_ENREF_5) [^20^](#_ENREF_20) and considering a rate of PNEN<2cm of 20%, we estimate an incidence of around 580 PNEN<2cm per year only in Europe. Worldwide the estimation of new PNEN<2 cm is around 29840 cases in five years. In the study period we aim to include at least 1000 patients during the study period.

# TREATMENT OF SUBJECTS

Study flowchart is provided in **Appendix 1**.

## 6.1 Diagnostic work-up before inclusion

The goal of the diagnostic work-up is to characterize the neoplasm and to rule out other lesions (i.e. ductal adenocarcinoma, accessory spleen, solid serous cystadenoma). This work-up should have taken place no more than 12 months prior to inclusion. A high quality cross-sectional imaging study, either Computed Tomography (CT) or Magnetic Resonance Imaging (MRI) is mandatory. Diagnosis has to be proven by a positive fine-needle aspiration (FNA) or by the presence of a measurable nodule on high-quality imaging technique (CT or MR) that is positive at 68Gallium DOTATOC-PET scan or Octreoscan. Patients who undergo surgery for NF-PNEN<2cm within 12 months can also be enrolled. In these cases, diagnosis has to be proven by histological confirmation of NF-PNEN. CgA should be determined at treating physician’s discretion.

**6.2 NF-PNEN management**

NF-PNEN management will be decided at the hospital and all therapeutics decision will be decided/coordinated by the treating physician.

Advised surveillance strategy consists of imaging studies (MR or EUS or US), every 6 months for the first two years and yearly thereafter for five years in the absence of significant changes on imaging or symptoms appearance. During surveillance, a high-quality imaging technique (MRI or CT) is mandatory at least every 12 months.

Determination of CgA during follow-up is at physician’s discretion. During follow-up, the treating physician is responsible for patient management and decision-making. If follow-up parameters change during follow-up, the decision for a more diagnostic work-up, surgery, or an intensified follow-up schedule is at the discretion of the treating physician (**Appendix 2**). If surgical resection is warranted, timing and type of resection will be established by the treating physician. Suggested scheme of follow up after surgery is depicted in **Appendix 3.**

Date of surgery does not change the timing of follow up which starts from the date of enrolment. If during surveillance a NF-PNEN size increases > 2 cm and surgery is not performed, the reason should be stated. In this case patient is not excluded and follow-up will continue regularly.

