# METHODS

## Study Endpoints

### Main study endpoint

### The primary endpoint is disease/progression-free survival, defined as the time from study enrolment to the first evidence of progression (surveillance group) or recurrence of disease (surgery group) or death from disease.

### Secondary study endpoints

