### To evaluate the frequency of asymptomatic sporadic NF-PNEN ≤ 2 cm among overall sporadic NF-PNEN. Participating centers are required to give yearly the number of patients with NF-PNEN referred to their institution.

### The outcome of patients with an indication for NF-PNEN resection, in terms of the number of operated patients, surgical procedures, morbidity, mortality, and NF-PNEN recurrence.

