# STATISTICAL ANALYSIS

The first analyses will regard the data collected within the first 2 years. This report will contain purely descriptive statistics, according to the study endpoints described. The second analysis, after 5 years, will give an update of the first report and provide a more in depth analysis of the primary and secondary study endpoints.

Baseline patient and NF-PNEN characteristics will be described. Also, descriptive of the primary and secondary endpoints will be given. Depending on distributional properties of the observed variable, percentages, means ± standard deviation (SD), or medians with interquartile ranges (IQR) will be reported. Statistical significance will be assessed with use of the Student’s t-test for normally distributed continuous data; either the chi-square test for categorical data (with Yates’ correction when appropriate) or Fisher exact test for categorical data; and the median test for non-normally distributed continuous data. All reported p-values will be two-sided and a value < 0.05 will be considered to be significant. Data will be analysed with SPSS (SPSS Inc, Chicago, Illinois). For the primary endpoints, univariate comparisons will be conducted, to identify individual patient and NF-PNEN risk factors for progression/recurrence. As primary potential risk factors are considered; 1. NF-PNEN size at initial diagnosis, 2. NF-PNEN growth during follow-up, 3. serum CgA, 4.. Patient age, 5. Ki67.

Outcomes will be evaluated in the intention-to-treat population on the basis of treating physician-assessed tumor progression/recurrence. Survival analysis techniques and Cox regression with time-dependent recurrent covariates measures will be applied. Progression/recurrence is defined according to Response Evaluation Criteria in Solid Tumors (RECIST)[^23^](#_ENREF_23) version 1.0 criteria. In the surveillance group progression is defined as the appearance of distant metastases and/or local signs of invasiveness (I.e. vascular or nearby organs invasion). The mere tumor size increasing will be not considered a sign of progression unless it reaches > 2 cm of maximum diameter. The two groups of patients (active surveillance and surgical resection group) will not be directly compared. Rate of expect events is 0-10% for the two groups^19^ .

Multivariate survival analysis will only be performed if the number of events will be > 30. The potential risk factors, given above, will have first interest.

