**MANDATORY**

CT scan or MRI

^68^Gallium PET/CT Or Octreoscan

EUS+FNA

CgA + HADS + EORTC QLQ-C30 v3 and GI.NET21

Or histological confirm of NF-PNEN ≤ 2 cm

UPFRONT SURGERY OR ENROLLMENT*

* Date of surgery does not chance the timing of follow up that starts from the date of enrolment.

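### Recurrence after surgery is timed from enrolment, although patients may enrol after surgery or be operated on at any time later, and group membership after a switch is undefined

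*Protocol*

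**What the plan says.** **Time origin.** The main study endpoint (Methods, Study Endpoints) is disease/progression-free survival, "defined as the time from study enrolment to the first evidence of progression (surveillance group) or recurrence of disease (surgery group"), with death from disease as the remaining event. Enrolment is therefore the origin for recurrence in operated patients. Section 6.2 states "Date of surgery does not change the timing of follow up which starts from the date of enrolment", and the schemes in Appendices 2 and 3 repeat it as a footnote.

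**Entry after surgery.** Section 6.1 states "Patients who undergo surgery for NF-PNEN<2cm within 12 months can also be enrolled" and continues "In these cases, diagnosis has to be proven by histological confirmation of NF-PNEN". The inclusion criteria in section 5.2 say the same. The first box of Appendix 3 is labelled "UPFRONT SURGERY OR ENROLLMENT".

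**Surgery after entry.** Section 6.2 leaves surgery during surveillance to the treating physician and sets no time limit.

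**Surgical outcomes.** A secondary endpoint reports patients with an indication for resection "in terms of the number of operated patients, surgical procedures, morbidity, mortality, and NF-PNEN recurrence".

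**Analysis.** The Statistical Analysis section says "Outcomes will be evaluated in the intention-to-treat population". Growth of a surveilled tumour counts as progression only beyond 2 cm. Metastasis and local invasion also count. The same section says that the surveillance and surgery groups will not be directly compared.

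**The concern.** Recurrence can occur only after resection, so its natural origin is the date of surgery. The protocol uses enrolment, which may fall before, at or after surgery. Two separate distortions follow, in different patients.

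- **Operated on after enrolment.** The time between enrolment and surgery cannot contain a recurrence but is counted as recurrence-free (immortal time).
- **Enrolled after surgery.** These patients had to survive and consent before they could enter. Operative deaths and early recurrences before that point are never seen (left truncation).

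A third difficulty is group membership. Nobody is assigned a treatment, so intention-to-treat has nothing to refer to, and the protocol does not say whether a surveillance patient who is later resected stays under surveillance or joins the surgery group. If such patients stay, a removed nodule can no longer reach the event of growth beyond 2 cm.

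At stake are the recurrence estimate for operated patients, operative mortality, the progression estimate under surveillance, and the models of risk factors for progression or recurrence. With events expected in only 0-10% of each group, small absolute errors are large relative ones.

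**Working it through.** The protocol gives no figure that can be reproduced here, and the size of the bias cannot be computed from it. The figures below are illustrations. The only input from the protocol is the 0-10% range of expected events. It states no time horizon, so 10% at 5 years after surgery is an assumption.

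**1. Surgery after enrolment.** Assume constant hazard and a true 5-year risk of 10%. If surgery is s years after enrolment, only 5 − s years are at risk by year 5 from enrolment, so apparent risk = 1 − 0.9^((5 − s)/5).

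| Surgery after enrolment | Calculation | Apparent 5-year risk |
|---|---|---|
| 3 months | 1 − 0.9^0.95 | 9.5% |
| 6 months | 1 − 0.9^0.90 | 9.0% |
| 12 months | 1 − 0.9^0.80 | 8.1% |
| 24 months | 1 − 0.9^0.60 | 6.1% |

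With Weibull cumulative hazard H(t) = −ln(0.9)·(t/5)^k, the range for 3 to 24 months is 9.8% to 7.8% for k = 0.5 and 9.3% to 4.8% for k = 1.5. The direction is the same for every shape.

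As a share of person-time: five years of recruitment plus at least one year of follow-up gives 1 to 6 years per patient, with mean 3.5 if accrual is uniform. The wait then makes up 0.25/3.5 = 7%, 0.5/3.5 = 14% and 1/3.5 = 29%. For surgery at 24 months it is 2/4 = 50%, because patients followed for more than two years have a mean of 4.

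**2. Patients who switch from surveillance.** Assume surgery uniform over 0.5 to 3 years after enrolment and a recurrence hazard of 2% per year. By year 3 from enrolment the time at risk is uniform over 0 to 2.5 years, so the risk is 1 − (1 − e^(−0.05))/0.05 = 2.5%. By year 3 from surgery it is 1 − e^(−0.06) = 5.8%. The gap arises because the first figure has 1.25 years at risk on average and the second has 3.

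**3. Recurrence in patients enrolled after surgery.** Use the same Weibull form, a true 5-year risk of 10%, and a clock started at entry. For entry at 12 months, apparent risk = 1 − S(6)/S(1).

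| Hazard after surgery | Entry uniform over 0-12 months | Entry at 12 months |
|---|---|---|
| Falling (k = 0.5) | 7.6% | 6.6% |
| Constant (k = 1) | 10.0% | 10.0% |
| Rising (k = 1.5) | 11.1% | 12.1% |

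The bias may go either way and is nil under constant hazard.

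**4. Operative mortality.** Assume a true 90-day mortality of 2%, deaths uniform over 90 days, and post-surgery entry uniform over 12 months. An operative death is observable only if entry precedes it, which has probability 45/365 = 12.3%. If a share f of operated patients would enter after surgery, reported mortality is about 2% × (1 − 0.877f), ignoring the small change in the denominator. That gives 1.6%, 1.1% and 0.7% for f = 25%, 50% and 75%. The sizes are assumed. The direction is not, because a patient who dies before enrolment cannot enter.

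**5. Progression under surveillance.** No rate of surgery is given, so no size can be stated. Section 6.2 lets changes at follow-up lead to surgery, and the Statistical Analysis section makes growth beyond 2 cm an event. Nodules removed before that threshold cannot reach it.

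**The case against.** **No comparison is planned.** This is the strongest objection, and it stands. A reader might infer that a surgery-versus-surveillance contrast is biased in favour of surgery, but the protocol excludes a direct comparison. Within-group estimates and risk-factor models are still affected, and because the stated aim is the most appropriate management, readers may set the two results side by side.

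**Intention-to-treat may mean management at enrolment.** On that reading switching patients stay under surveillance, and immortal time in the primary endpoint shrinks to the wait for upfront surgery (10% becomes 9.5% to 9.0% for 3 to 6 months). This stands as far as it goes, but the protocol does not define the term, and the recurrence part of the secondary surgical endpoint remains affected.

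**The sentence in section 6.2 concerns visits.** Read alone, it may. The endpoint definition itself fixes enrolment as the origin, so the point does not depend on that sentence.

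**This is detail for a statistical analysis plan.** Methods for delayed entry or competing events could be left there. The time origin could not, because the protocol states it.

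**The 12-month window has no stated reference point.** Correct. Entry after surgery is the natural reading, since histology is required and the preceding rule in section 6.1 limits the work-up to 12 months before inclusion. If the window ran forward from enrolment, steps 3 and 4 would fall away, and the surgery group would be defined by a later event.

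Two further inferences go too far. Recurrence in patients enrolled after surgery is not necessarily understated (step 3). Nor does a surveillance patient become event-free once resected, because metastasis or death from disease can still occur.

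**Conclusion.** The concern holds within limits. Enrolment is the wrong origin for recurrence in operated patients, and group membership after a switch is undefined.

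- **Recurrence, surgery after enrolment:** understated. A true 10% appears as 9.5% to 6.1% for surgery at 3 to 24 months, assuming constant hazard and a 5-year horizon.
- **Recurrence, enrolment after surgery:** direction unknown. The illustrated range is 6.6% to 12.1% against a true 10%, with no bias under constant hazard.
- **Operative mortality:** understated if patients enter after surgery. An assumed 2% would be reported as about 1.6% to 0.7%.
- **Progression under surveillance:** growth events are understated to the extent that nodules are removed before 2 cm. The size is not estimable from the protocol.

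This should be fixed before the main analysis. It does not invalidate a planned comparison, because there is none.

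**What to change.** In the endpoint definition and the Statistical Analysis section:

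1. Define group as the management recorded at enrolment, and either define intention-to-treat in those terms or drop it.
2. Time post-operative recurrence from the date of surgery, with delayed entry at enrolment for patients enrolled after surgery. Apply the same origin to surveillance patients resected later.
3. Estimate operative morbidity and mortality only in patients enrolled before surgery, and list the others separately.
4. For surveillance, run time from enrolment to progression with surgery as a competing event (cumulative incidence), and report progression-or-surgery alongside, so that the effect of removing nodules is visible.
5. State what the 12 months in the surgical inclusion criterion are measured from.

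These are changes of wording and analysis and leave patient management as it is. They need the enrolment and surgery dates. Section 6.3 lists the case record forms by title only, so confirm that both dates are captured. The main cost is fewer patients in the operative-mortality estimate. In addition, recurrence timed from surgery describes resected patients only, so anyone recorded for surgery at enrolment but never operated on must be counted separately.

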**6.3 Data collection**

Treating physicians will be asked to fill case record forms (CRF). The following CRF will be provided:

- CRF 1: Diagnostic work-up before inclusion
- CRF 2: Active surveillance outcomes
- CRF 3: Surgical outcomes
- CRF 4: Pathological findings
- CRF 5: Follow-up after surgery

Patients will be asked to fill a questionnaire regarding the burden of NF-PNEN (Hospital Anxiety and Depression Scale – HADS) and two questionnaires regarding quality of life of patients with NF-PNEN (EORTC QLQ-C30 - version 3.0 and EORTC QLQ-GI.NET21). All three module will be administered at initial diagnosis, during surveillance and during follow-up after surgery at each visit.[^21^](#_ENREF_21) [^22^](#_ENREF_22) **(Appendix 4, Appendix 5, Appendix 6).**

Data will be recorded by the treating physician on a specific web-based site. Patients demographics will be not included in the CRF, and every patient will have an unique code, assigned by the treating centre, that will identify the Centre and the patient itself (e.g. SR001 San Raffaele Hospital patient number 1).

# METHODS

## Study Endpoints

### Main study endpoint

### The primary endpoint is disease/progression-free survival, defined as the time from study enrolment to the first evidence of progression (surveillance group) or recurrence of disease (surgery group) or death from disease.

### Secondary study endpoints

### To evaluate the frequency of asymptomatic sporadic NF-PNEN ≤ 2 cm among overall sporadic NF-PNEN. Participating centers are required to give yearly the number of patients with NF-PNEN referred to their institution.

### The outcome of patients with an indication for NF-PNEN resection, in terms of the number of operated patients, surgical procedures, morbidity, mortality, and NF-PNEN recurrence.

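### The yearly count that centres must report does not fit the frequency endpoint: it is not limited to sporadic cases, and no numerator is collected apart from enrolled patients

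*Protocol*

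**What the plan says.** The Protocol, section 7 (Secondary study endpoints), states the aim: "To evaluate the frequency of asymptomatic sporadic NF-PNEN ≤ 2 cm among overall sporadic NF-PNEN". The sentence that follows sets the data requirement: "Participating centers are required to give yearly the number of patients with NF-PNEN referred to their institution". Sporadic disease is specified in the first sentence and not in the second.

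Other sections bear on what could serve as the numerator:

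- Section 5.3 excludes patients with a genetic syndrome, so hereditary cases never enter the cohort.
- Section 5.2 makes "Informed consent" a condition of entry. It also requires proof of diagnosis: positive FNA, a nodule positive on functional imaging, or histology in operated patients.
- Section 4 adds: "Study participation is voluntary".
- Section 6.3 lists five case record forms, beginning with "CRF 1: Diagnostic work-up before inclusion". The others cover surveillance, surgery, pathology and postoperative follow-up. All concern included patients. No screening or eligibility log is listed.
- Sections 5.2 and 6.1 contain a 12-month window, for the age of the diagnostic work-up and for operated patients.

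**The concern.** A proportion needs a numerator and a denominator drawn from the same population over the same period. Here the endpoint is defined within sporadic disease, while the reported count is worded for all NF-PNEN. Nothing asks how many referred patients were asymptomatic with a tumour of at most 2 cm, whether or not they joined.

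If enrolments fill that gap, the reported frequency depends partly on consent, diagnostic proof and recruitment effort at each centre as well as on case mix. The share of eligible patients who were enrolled also stays unknown. A reader needs that share to judge how selected the cohort is, since participation is voluntary.

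A statistical analysis plan could choose an estimator later, but it could not recover counts that centres were never asked to gather. The point therefore belongs in the Protocol.

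**Working it through.** The Protocol states no expected value or precision for this endpoint, so there is no figure of its own to reproduce. The 20% in section 5.4 is a planning share of small tumours among all PNEN, which is a different quantity.

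**Notation.** For the patients referred over the study period:

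- N = all NF-PNEN referred (the count required in section 7).
- h = hereditary share of N. Not given; assumed 5% to 20%.
- S = N(1 − h) = sporadic NF-PNEN referred.
- p = true frequency, so pS patients are sporadic, asymptomatic and at most 2 cm.
- c = share of those pS patients who are enrolled, after consent and proof of diagnosis. Not given; assumed 50% to 100%.

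**Endpoint as defined:** pS / S = p.

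**Ratio obtainable on a literal reading:** c·pS / N = p × c(1 − h).

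**Factor c(1 − h):**

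| h | c = 100% | c = 80% | c = 50% |
| --- | --- | --- | --- |
| 0% (count read as sporadic only) | 1.00 | 0.80 | 0.50 |
| 5% | 0.95 | 0.76 | 0.475 |
| 10% | 0.90 | 0.72 | 0.45 |
| 20% | 0.80 | 0.64 | 0.40 |

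As an illustration, take an assumed true frequency of 30% and h = 10%. The ratio would read 0.30 × 0.90 = 27% at c = 100%, 0.30 × 0.72 = 21.6% at c = 80%, and 0.30 × 0.45 = 13.5% at c = 50%.

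**Look-back.** Enrolments may include patients referred before the first counted year. Let L be the resulting inflation of the numerator, so that the factor becomes c·L(1 − h). With 12 months of look-back on 5 years of recruitment (section 4), L is at most 6/5 = 1.2. This treats the age limit on the work-up as a limit on the time since referral, which is an assumption. The factor exceeds 1 only if c > 1 / [1.2(1 − h)]:

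- h = 0%: c above 0.833
- h = 5%: c above 0.877
- h = 10%: c above 0.926
- h = 16.7%: c would have to exceed 1.000, which is impossible; the same holds for any larger h

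**After the fix.** With sporadic cases as the denominator, all asymptomatic cases of at most 2 cm as the numerator whether enrolled or not, and one common period, h = 0, c = 1 and L = 1. The factor is then 1.00.

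**The case against.** The strongest reply is that the defects are partly inferred. The count sentence directly follows the endpoint and exists to serve it, so a centre could reasonably take it to mean sporadic cases only. The Protocol does not say that hereditary cases are to be counted, nor does it say that enrolled patients form the numerator. This stands as far as it goes. The supported statement is that the count is not limited to sporadic cases and that no numerator is named. On the sporadic-only reading h becomes 0 and the denominator problem disappears, but the numerator problem remains (the 0% row of the table). If centres differ in their reading, their counts will not be comparable.

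A reader might also infer that the frequency is certain to be too low. The documents do not support certainty. The 12-month windows in sections 5.2 and 6.1 can raise the numerator, and the cap of 1.2 on that effect is itself assumed, because section 6.1 limits the age of the work-up and not the time since referral. Downward is the expected direction, because incomplete enrolment and hereditary cases in the count both lower the ratio.

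Nor would the ratio reflect recruitment effort alone. On the formula above it varies with both p and c.

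Finally, the impact is limited. This is one secondary endpoint, and it does not feed the primary endpoint, the risk-factor analyses in section 8 or the recruitment target in section 5.4.

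**Conclusion.** The point holds. As written, the data requirement does not deliver the stated endpoint: a literal reading yields enrolled patients over all NF-PNEN referred. Without look-back, the discrepancy is a factor of 0.95 to 0.40 for h of 5–20% and c of 50–100%. Both ranges are assumptions, so they illustrate the formula and are not evidence about this study's actual bias.

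The conclusion rests on enrolments being the numerator, which follows from the absence of any other source in the Protocol. If the sponsor intends another source, the Protocol should name it. Even if look-back happened to offset the loss, the result would still be a different quantity from the endpoint. The correction should be made, since a stated endpoint depends on it, but nothing in the primary analysis changes.

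**What to change.** In section 7, replace the single yearly count with three counts per centre, all for the same calendar period:

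1. sporadic NF-PNEN patients referred, of any size;
2. of these, the number asymptomatic with a tumour of at most 2 cm, regardless of consent or enrolment;
3. of these, the number enrolled.

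Define the frequency as (2)/(1), and report (3)/(2) as the enrolment fraction. Keeping referral as the basis leaves the counted population as the Protocol has it, apart from the restriction to sporadic cases.

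The cost is two additional aggregate numbers per centre per year, with no individual records sent to the lead centre. The real work is local: centres must classify every referred patient, including those who do not take part, by hereditary status, symptoms and size. The Protocol mentions no existing centre-level form for the yearly count, so one may have to be drawn up.
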